### Study design

The study was designed according to the Standard Protocol Items: Recommendations for Interventional Trials (SPIRIT) 2013 checklist. After recruitment, participants will enter into a 2-week run-in period, during which general information on diet, physical activity, type and dosage of medications will be obtained. All measurements, including anthropometric and biochemical assessments, will be made at this stage, and then participants will be stratified based on age (20–40 and 40–60 years), gender (male/female), body mass index (18.5–24.9 and 25–30), and type of medicines (anti-inflammatory and immunosuppressant) into different strata. Actually, first we will enroll a participant who meets the inclusion criteria in a stratum. Then, based on these variables the second person, who is matched with the first one in that stratum would be gone to the same stratum. So, we would have two similar persons (in terms of the aforementioned variables) in a stratum. Then, the two persons in a single stratum would be randomly assigned into the intervention and non-intervention groups. Therefore, we would have 15 strata (each consisting of two similar persons) in total and then individuals in the strata would be randomly allocated to the aforementioned groups. So, we would have 15 people in each group and the groups would be almost similar in terms of these variables. A person who is not part of the study will randomly allocate participants. Participants in the intervention group will receive a low-FODMAP diet according to their usual dietary intakes, whereas participants in the control group will receive their usual diet without any modification, for 4 weeks. Participants in both groups will receive the usual dietary recommendations for patients with IBD. To evaluate participants’ compliance, three 24-h dietary recalls will be taken throughout the intervention. Participants will be asked not to change their life-style and medicines during the study. Again, all measurements will be examined at the end of trial.

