### Statistical analysis

Normality of data will be examined using the Kolmogorov-Smirnov test. Continuous variables will be compared between the two groups by the independent sample *t* test, whereas the chi-square test will be used to compare categorical variables. Normally distributed continuous variables will be reported as mean ± SD, and as median and IQR if they are not normally distributed; categorical data will be reported as absolute and relative percentage frequencies. The effect of the study intervention on desirable outcomes will be measured using the independent sample *t* test for normally distributed data and the Wilcoxon test for non-normally distributed data. We will adjust our final results for potential confounding factors using multivariable regression modeling. Statistical analyses will be done using SPSS, version 21. *P* values <0.05 will be considered statistically significant.

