### Strengths

This is the first clinical trial investigating the effect of a low-FODMAP diet on the intestinal microbiota and inflammation in patients with IBD. Stratified randomization of participants is another strength, which minimizes confounding problems in this randomized controlled trial (RCT). In addition, we will examine the effect of a low-FODMAP diet on different clinical symptoms in patients with IBD. Another strength of the current study is the acquisition of a set of data from participants during the run-in period. Moreover, we will obtain data from participants about dietary intakes and physical activity during the intervention. Finally, along with serum cytokine levels, fecal calprotectin is an important clinically relevant indicator of intestinal inflammation.

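### Patients are randomised within 15 matched pairs, but the named test ignores the matching; if the matching factors predict the outcome, that test is conservative and leaves available precision unused

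*Protocol article*

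**What the plan says.** All references are to the protocol article.

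- **Study design, matching factors:** "participants will be stratified based on age (20–40 and 40–60 years), gender (male/female), body mass index (18.5–24.9 and 25–30), and type of medicines".
- **Study design, allocation:** "Then, the two persons in a single stratum would be randomly assigned into the intervention and non-intervention groups". The count follows: "Therefore, we would have 15 strata (each consisting of two similar persons) in total". The stated aim is balance: "So, we would have 15 people in each group and the groups would be almost similar in terms of these variables".
- **Statistical analysis, effect of the diet:** "The effect of the study intervention on desirable outcomes will be measured using the independent sample" *t* test if the data are normal, and otherwise by a Wilcoxon test whose type (rank-sum or signed-rank) is not given.
- **Statistical analysis, adjustment:** "We will adjust our final results for potential confounding factors using multivariable regression modeling". No covariate is named.
- **Study sample size calculation:** the formula is of the type for two independent groups and has no term for correlation within pairs.
- **Strengths:** "Stratified randomization of participants is another strength, which minimizes confounding problems".

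**The concern.** The randomisation has a structure that the named test leaves out. One-to-one allocation inside matched pairs removes between-pair variation from the treatment contrast, whereas the independent-sample t test still counts that variation in its standard error. If pair members resemble each other on the outcome, the standard error is too large, the confidence interval too wide and the type I error below its nominal 5%.

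At stake is precision in a trial of 15 per arm. With the protocol's own SDs and difference, the independent t test has about 70% power before any drop-out, against a target of 80%. The protocol also presents the stratified allocation as a strength because it limits confounding. A factor can confound only if it predicts the outcome, and that is the situation in which leaving it out of the analysis costs something.

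**Working it through.** **Inputs.** From Study sample size calculation: S1 = 25.88, S2 = 21.99, means 26.6 and 4 (difference 22.6), two-sided 5% level, 80% power, 10% drop-out. From Study design: 15 pairs. The within-pair correlation ρ is not in the document; it is an assumption, shown from 0 to 0.5.

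**The plan's own figure.** S1² + S2² = 669.77 + 483.56 = 1153.33. The formula as printed gives (1.96 + 0.8416)² × 1153.33 / (26.6² − 4²) = 7.849 × 1153.33 / 691.56 = 13.09. Dividing by 0.9 gives 14.54, so 15 per group reproduces. ρ does not enter. (The printed denominator is a separate matter: with (26.6 − 4)² = 510.76 the result is 17.72 before drop-out. That is why the baseline power below is 70% and not 80%.)

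**Standard errors with 15 complete pairs.**
- Independent t test (28 df): √(1153.33 / 15) = 8.77, whatever ρ is.
- True standard error under pair randomisation: √((1153.33 − 2ρ × 25.88 × 21.99) / 15) = √((1153.33 − 1138.20ρ) / 15).
- Example at ρ = 0.3: √((1153.33 − 341.46) / 15) = 7.36, and 8.77 / 7.36 = 1.19.

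Type I error is from simulation of bivariate normal pairs. Power is for a difference of 22.6.

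| ρ (assumed) | True SE | SE overstated by | True type I error, independent t | Power, independent t | Power, paired t (14 df) |
|---|---|---|---|---|---|
| 0 | 8.77 | 0% | 5.0% | 70% | 67% |
| 0.1 | 8.32 | 5% | about 4% | 71% | 71% |
| 0.2 | 7.86 | 12% | about 3% | 72% | 76% |
| 0.3 | 7.36 | 19% | 2.2% | 73% | 81% |
| 0.5 | 6.24 | 41% | 0.9% | 76% | 92% |

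With no drop-out, pairing breaks even at ρ of about 0.07 for power and 0.09 for interval width.

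**Adding the planned 10% drop-out.** A strict paired test loses the partner of every patient who leaves. Simulated power with independent 10% drop-out, independent against paired: 65% v 56% at ρ = 0; 65% v 60% at 0.1; 66% v 65% at 0.2; 67% v 71% at 0.3. The paired test's advantage at 0.2 is gone.

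**Covariate model under the same drop-out.** Four binary factors, shared within pairs, with equal additive effects and a common SD of √(1153.33 / 2) = 24.0. The comparison is the t test against the same contrast adjusted for the four factors; baseline value is in neither.

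| Outcome variance explained by the factors | Change in power from adjusting |
|---|---|
| 0% | about −2 points |
| 10% | about +3 points |
| 20% | about +7 points |
| 30% | about +12 points |

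Type I error of the adjusted analysis stayed near 5% throughout.

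**The case against.** **The matching does its job without a paired analysis.** This stands. Balance is the stated purpose, and the independent test's own power rises with ρ (70% to 76% above) because the arms are balanced. A reader might infer that the matching is wasted; the documents do not support that. Only the further precision goes unused.

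**The excess depends on an unknown.** This stands too. A reader might infer that the standard errors are too large whatever the data show, but at ρ = 0 there is no excess. Pairs share only two-level bands, sex and medicine class, and the primary outcome is a change from baseline. Nothing in the protocol shows that these factors explain 30% or 50% of the variance in that change, so the upper rows of the table are scenarios and not expectations.

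**A paired test would be worse after drop-out.** Correct for low ρ, as shown, and the protocol also excludes patients after allocation for medicine changes, hospitalisation or infection. This rules out a paired t test or signed-rank test as primary. It does not count against a model that keeps unpaired patients.

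**The regression could already contain the matching factors, and its covariate list may sit in a document not shown.** Partly stands. It could contain them, but the protocol does not commit to it, and the test it does name for the treatment effect leaves the design out. The point rests on that stated mismatch and not on a missing list.

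**The Wilcoxon wording is clear enough.** Largely accepted. Set beside the independent t test, rank-sum is the natural reading; in a pair-randomised trial it is still worth a word to say so.

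**Conclusion.** The mismatch is real and its consequence is conditional. Allocation is within matched pairs, and the named analysis of the treatment effect treats the arms as unrelated. If the matching factors are prognostic, the t test is conservative: for an assumed within-pair correlation of 0.1 to 0.5 its standard error is 5% to 41% too large and its true type I error about 4% down to 0.9%. If they are not prognostic, there is no excess.

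A reader might infer a risk of false-positive findings. Under positive correlation the error runs the other way. Only a negative correlation would inflate type I error (about 7% at −0.2), and nothing in the protocol suggests one.

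The figures assume normal outcomes, the protocol's SDs and a difference of 22.6. This should be corrected because the remedy is cheap and the trial has little power to spare; it does not invalidate the comparison.

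**What to change.** Name one primary analysis that carries the randomisation structure: a linear model of the week-4 value on treatment and baseline value, with age band, sex, BMI band and medicine class as four binary covariates. Pair as a random effect is the alternative. Either keeps a patient whose partner drops out. The covariate version spends 4 degrees of freedom, whereas the paired t test goes from 28 to 14.

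Do not make a strict paired t test or signed-rank test primary. If a rank-based check is kept, state whether it is the rank-sum test or the signed-rank test on within-pair differences.

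The cost is analysis wording and a few degrees of freedom: about 2 points of power if the factors are non-prognostic, against a gain of about 3 to 12 points if they explain 10% to 30% of outcome variance. Trial status reports recruitment as complete, so the choice should be recorded and dated before the arms are compared.

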### Patient and public involvement

Patients and the public were not involved in the development of this study.

### Intervention

A 2-week dietary menu will be provided for each participant. First, we will calculate the basic metabolic rate (BMR) of each subject according to the participant’s age, sex, height and current weight, using the Harris-Benedict formula. Then, daily energy requirements of each participant will be estimated based on participants’ physical activity and the thermogenic effect of foods (TEF). Based on the total energy requirement of each individual, we will design a diet consisting of 55% of total energy from carbohydrates, 25% from fats, and 20% from proteins. Then a menu cycle will be written considering the foods high in FODMAP, which will be restricted in these menu cycles. All dietary menus would be designed to include six daily meals, including three main meals and three snacks.

### Assessment of study outcomes

#### Primary outcomes

The main primary outcomes in the current study would be fecal calprotectin and lactoferrin as well as gut microbiota including Clostridium cluster IV, *Faecalibacterium prausnitzii*, Rosburia spp., Lactobacillus spp., Bifidobacteria spp., *Akkermansia muciniphila*, *Bacteroides fragilis*, and Ruminococcus spp. and the *Firmicutes* to *Bacteroidete*s ratio.

To examine gut microbiota and fecal calprotectin and lactoferrin, stool samples (10 g) from one defecation will be taken from each individual at study baseline and end of trial. The samples will be immediately stored at − 20 C° until further analysis. Bacterial DNA will be extracted using the QIAamp (QIAGEN) commercial fecal DNA kit. Calprotectin is a calcium binding protein commonly derived from neutrophils and monocytes and in to a lesser extent from macrophages [15]. Calprotectin is found in stool and plasma, and its concentration increases throughout inflammatory conditions including IBD, and infection [15, 16]. The quantity of intestinal microbiota including Clostridium cluster IV, *F. prausnitzii*, Rosburia spp., Lactobacillus spp., Bifidobacteria spp., *A. muciniphila*, *B. fragilis*, and Ruminococcus spp., as well as the *Firmicutes* to *Bacteroidetes* ratio, will be determined using commercial real-time PCR kits (QIAamp, QIAGEN). In addition, fecal concentrations of calprotectin and lactoferrim will also be measured using an enzyme-linked immunosorbent assay. Therefore, our primary outcomes will be the mean difference in changes from baseline to 4-week follow up in calprotectin concentrations and quantity of gut microbiota between the intervention and control groups.

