### Study sample size calculation

By considering a type I error of 5% (α = 0.05) and type II error of 20% (β = 0.20, power = 80%) and the primary outcome variable of expected difference between the intervention and control groups in mean fecal calprotectin, calculated based on the two sided *t* test, we calculated the required sample size using the following formula:
$$ n=\frac{{\left({\mathrm{Z}}_{1-\frac{\alpha }{2}}+{\mathrm{Z}}_{1-\beta}\right)}^2\times \left({S_1}^2+{S_2}^2\ \right)}{\left({\upmu_1}^2-{\upmu_2}^2\right)} $$

(S1= 25.88, S2= 21.99, μ1= 26.6, μ2= 4)

Based on this formula and allowing for 10% drop-out in each group, we will need a sample size of 15 persons for each group.

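### Eleven outcomes are labelled primary and held to an unqualified P<0.05 (ten in the section's closing sentence), while the trial is sized on fecal calprotectin alone

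*Protocol article*

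**What the plan says.** All references are to the protocol article.

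- **Primary outcomes, opening sentence:** "The main primary outcomes in the current study would be fecal calprotectin and lactoferrin as well as gut microbiota including Clostridium cluster IV". The list continues with seven further bacterial groups and the Firmicutes to Bacteroidetes ratio. The count is 2 fecal markers + 8 bacterial groups + 1 ratio = 11.
- **Primary outcomes, closing sentence:** "our primary outcomes will be the mean difference in changes from baseline to 4-week follow up in calprotectin concentrations and quantity of gut microbiota", compared between the two groups. Lactoferrin is absent. Counting the ratio as part of the microbiota, this leaves 10.
- **Study sample size calculation:** the trial is sized on "the primary outcome variable of expected difference between the intervention and control groups in mean fecal calprotectin", with a two-sided type I error of 5% and 80% power. The result is 15 per group after a 10% allowance for drop-out.
- **Statistical analysis:** "The effect of the study intervention on desirable outcomes will be measured using the independent sample" t test, or the Wilcoxon test for non-normal data. P "values <0.05 will be considered statistically significant". The sentence does not distinguish primary from other outcomes.

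**The concern.** With 11 outcomes carrying the same primary label and the same threshold, any one of them can be reported as a positive primary result. A single taxon reaching P<0.05 would qualify even if calprotectin, the only outcome with a power calculation, showed nothing. The Discussion anticipates effects on both inflammation and bacterial growth, so either kind of result would read as confirmation. The two sentences on lactoferrin also leave it open whether a significant lactoferrin result would count as primary. If this is settled after the results are known, the choice will not be credible.

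**Working it through.** **Inputs from the protocol article.** k = 11 primary outcomes (10 on the closing sentence); threshold 0.05 per test; S1 = 25.88, S2 = 21.99, μ1 = 26.6, μ2 = 4; 15 per group; 10% drop-out. **Assumed:** a common correlation ρ between outcomes, from 0 to 0.9, because the documents give none.

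**1. The plan's own figure.** With the formula as printed:

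n = (1.960 + 0.842)² × (25.88² + 21.99²) / (26.6² − 4²) = 7.849 × 1153.33 / 691.56 = 13.09, and 13.09 / 0.9 = 14.5, rounded up to 15.

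The stated 15 is reproduced, for calprotectin only and with the full 0.05. The printed denominator is a difference of squares. The usual denominator, (26.6 − 4)² = 510.76, gives 17.7, so 18 per group, or 20 with drop-out. That is a separate matter, but it affects the power figures in step 3.

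**2. Chance of at least one false primary result if the diet has no effect.**

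Independent tests: 1 − 0.95¹¹ = 0.431, and 1 − 0.95¹⁰ = 0.401.

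Common correlation ρ: 1 − ∫ φ(x) [Φ((1.96 − √ρ·x)/√(1−ρ)) − Φ((−1.96 − √ρ·x)/√(1−ρ))]ᵏ dx, integrated numerically.

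| ρ | 11 outcomes | 10 outcomes |
|---|---|---|
| 0 | 43.1% | 40.1% |
| 0.3 | 37.5% | 35.1% |
| 0.5 | 30.4% | 28.7% |
| 0.7 | 22.3% | 21.3% |
| 0.9 | 13.1% | 12.8% |

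A simulation of t tests with 15 per group and 11 outcomes (20,000 replicates) gave 43.0%, 37.8%, 31.3% and 22.8% at ρ = 0, 0.3, 0.5 and 0.7, within about one percentage point.

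**3. Power for calprotectin under each remedy.** Standardised difference: 22.6 / √(1153.33/2) = 22.6 / 24.01 = 0.94. Two-sided t test (noncentral t), 15 per group:

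- at 0.05: 70% (67% with 14 per group, 63% with 13);
- at 0.05/11 = 0.00455: 33%.

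Bonferroni over 11 would need 31 per group for 80% power by the normal formula, or 35 with drop-out.

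**The case against.** The case on the other side has several parts.

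- **An adjustment may be stated elsewhere.** The article condenses a fuller protocol, and a testing order or multiplicity adjustment is commonly left to an analysis plan. That stands: a reader might infer that the trial has no such rule anywhere, and the article cannot show this. What the article itself fixes is the primary list, its inconsistency on lactoferrin and an unqualified threshold.
- **The sample size section is not a third list.** A reader might infer that three places give three different primary sets. The sample size section names the variable used for sizing, and sizing on one of several primary outcomes is not a contradiction. The one clear mismatch is lactoferrin. It may be loose shorthand, since the same section describes its assay.
- **No trial-wide 5% is claimed.** The 5% is stated for the calprotectin calculation and holds for that comparison. It would be wrong to say that a declared overall error rate is breached.
- **The error range rests on assumption.** No value in the table is a floor, since stronger correlation lowers it further. The figures also assume that each test has its nominal size. Patients are randomised within matched pairs but compared with independent-sample tests, so positive within-pair correlation would make each test's true size less than 5%.
- **The power loss must be measured from the right baseline.** A reader might infer that Bonferroni takes power from 80% to 33%. At the protocol's inputs the unadjusted figure is about 70%.
- **Microbiota is in the title and the aim, and recruitment is complete.** This bears on how the change is made. It does not justify leaving 11 primary outcomes on equal terms. Splitting alpha between an inflammation family and a microbiota family would also control error, but it gives calprotectin less than the 5% it was sized on.

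**Conclusion.** The point holds. Read as written, the article gives 11 outcomes primary status at P<0.05 each and contradicts itself on whether lactoferrin is one of them. If the diet has no effect, the chance of at least one nominally significant primary result is 43% under independence and 22% at an assumed common correlation of 0.7. Even at 0.9 it is 13%, more than twice the level of a single test. Dropping lactoferrin does not change the conclusion (40% and 21% at correlations of 0 and 0.7). These figures rest on no effect on any outcome, a common correlation that the documents do not supply, and exact 5% size for each test. Because the issue decides which result the trial may present as its main finding, it should be settled before analysis.

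**What to change.** In a dated, justified amendment made before analysis:

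1. Name the between-group difference in change from baseline to 4 weeks in fecal calprotectin as the single primary outcome, tested at two-sided 0.05. This follows the trial's own sizing.
2. Make lactoferrin, the eight bacterial groups and the Firmicutes to Bacteroidetes ratio key secondary outcomes, with Holm or Benjamini-Hochberg control across these ten. The microbiota outcomes then stay as a prespecified, error-controlled family, consistent with the title and aim.
3. Make the opening and closing sentences of the Primary outcomes section agree.

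The cost is a short change of text, but timing matters. Recruitment closed on 30 May 2019, and a 2-week run-in plus 4 weeks of diet would normally end follow-up about six weeks later, before publication in February 2020. The Data Availability statement says that no datasets had been generated or analyzed, so on the article's own account the change was still possible. If analysis has begun, the change should be reported as made after that point.

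The scientific cost is that a single-taxon result cannot be headlined as primary and needs stronger evidence. The first Holm threshold is 0.05/10 = 0.005, at which an outcome with the same standardised difference of 0.94 would have about 34% power with 15 per group. The change also leaves calprotectin at about 70% power, so the stated 80% has to be addressed separately.

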#### Secondary outcomes

The main secondary outcome variables in the current study will be serum concentrations of highly sensitive-C reactive protein (hs-CRP), tumour necrosis factor-α (TNF-α) and IL-1β. After 12 h of fasting, a 10-cc blood sample will be taken from each patient at study baseline and end of trial. Total cell blood counts (CBC), hemoglobin and hematocrit concentrations will be measured by a cell counter. Erythrocyte sedimentation rate (ESR) will be measured using the Wintergreen method. Then, serum will be isolated from the whole blood and stored at − 80 C^0^. Serum levels of inflammatory cytokines, including hs-CRP, TNF-α, and IL-1β will be measured by a commercial ELISA kit. CRP is produced almost exclusively in liver and by hepatocytes in response to pro-inflammatory cytokines such as IL-6, TNF-α, and IL-1. It is a reactive acute-phase protein with a short half-life [17]. A significant association has been found between the severity of IBD [18] and hs-CRP, TNF-α, and IL-1β. Therefore, our secondary outcomes will be the mean difference between the intervention and control groups in changes in hs-CRP, TNF-α, and IL-1β from baseline to 4-week follow up.

